## Abstract

**Background:**

The estimated annual global burden of miscarriage is 33 million out of 210 million pregnancies. Many women undergoing miscarriage have surgery to remove pregnancy tissues, resulting in miscarriage surgery being one of the most common operations performed in hospitals in low-income countries. Infection is a serious consequence and can result in serious illness and death. In low-income settings, the infection rate following miscarriage surgery has been reported to be high.

Good quality evidence on the use of prophylactic antibiotics for surgical miscarriage management is not available. Given that miscarriage surgery is common, and infective complications are frequent and serious, prophylactic antibiotics may offer a simple and affordable intervention to improve outcomes.

**Methods:**

Eligible patients will be approached once the diagnosis of miscarriage has been made according to local practice. Once informed consent has been given, participants will be randomly allocated using a secure internet facility (1:1 ratio) to a single dose of oral doxycycline (400 mg) and metronidazole (400 mg) or placebo. Allocation will be concealed to both the patient and the healthcare providers. A total of 3400 women will be randomised, 1700 in each arm. The medication will be given approximately 2 hours before surgery, which will be provided according to local practice. The primary outcome is pelvic infection 2 weeks after surgery. Women will be invited to the hospital for a clinical assessment at 2 weeks. Secondary outcomes include overall antibiotic use, individual components of the primary outcome, death, hospital admission, unplanned consultations, blood transfusion, vomiting, diarrhoea, adverse events, anaphylaxis and allergy, duration of clinical symptoms, and days before return to usual activities. An economic evaluation will be performed to determine if prophylactic antibiotics are cost-effective.

**Discussion:**

This trial will assess whether a single dose of doxycycline (400 mg) and metronidazole (400 mg) taken orally 2 hours before miscarriage surgery can reduce the incidence of pelvic infection in women up to 2 weeks after miscarriage surgery.

**Trial registration:**

Registered with the ISRCTN (international standard randomised controlled trial number) registry: ISRCTN 97143849. (Registered on April 17, 2013).

**Electronic supplementary material:**

The online version of this article (10.1186/s13063-018-2598-3) contains supplementary material, which is available to authorized users.

## Background

The estimated annual global burden of miscarriage is 33 million out of 210 million pregnancies [1, 2]. The majority of women with a miscarriage will undergo surgery, performed to remove pregnancy tissues from the uterus [3]. In many hospitals in low-income countries, miscarriage surgery is one of the most common operations performed; for example, at Queen Elizabeth Central Hospital, Malawi, an average of 156 suction evacuations for miscarriage are carried out each month, representing 68% of gynaecology admissions [4].

Infection is a serious consequence of miscarriage surgery. The data available from high-income countries found that it occurred in up to 6% of women following surgical management of miscarriage [5, 6]. In low-income settings, the infection rate after miscarriage surgery has been reported to be up to 30% [7]. Infection after miscarriage can result in serious illness and death, as well as long-term consequences from pelvic scarring, increased rates of ectopic pregnancy and infertility. Ectopic pregnancies can result in death from severe haemorrhage, and infertility has profound social and economic effects that go beyond childlessness, with women bearing the brunt of the burden [8].

For surgical termination of pregnancy, the standard practice is to provide prophylactic antibiotics before or during surgery as there is evidence of benefit for this intervention [9] and unanimous endorsement from policymakers and practitioners [9–13]. However, evidence is insufficient for miscarriage management and therefore, unsurprisingly, policymakers do not recommend, and practitioners do not consistently provide, prophylactic antibiotics during surgery. However, given that miscarriage surgery is common, and infective complications are frequent and serious, prophylactic antibiotics, if found to be effective in a well-conducted and adequately powered trial, may offer a simple and affordable intervention to reduce the burden of disease in low-income countries.

## Methods/Design

### Aims and objectives

The primary objective is to test the hypothesis that, in women having miscarriage surgery, pre-surgery prophylactic antibiotics (oral doxycycline 400 mg and oral metronidazole 400 mg) reduce the risk of pelvic infection within 14 days of surgery. In cases where participants do not return for follow-up within this period, follow-up until 28 days will be acceptable.

The secondary objectives are to test whether prophylactic antibiotics result in a reduction in maternal mortality, duration of clinical symptoms, hospital admission, unplanned consultations and overall antibiotic use. We will also examine the individual components of the primary outcome and test the hypothesis that prophylactic antibiotics, compared to placebo, do not incur serious adverse effects to the mother.

We will explore differential effects of antibiotic prophylaxis in the subgroups of (1) type of surgery (manual vacuum aspiration, suction curettage or sharp curettage), (2) type of miscarriage (incomplete or missed), (3) gestational age (< 12 weeks or ≥ 12 weeks, when known), (4) HIV status (positive or negative, when results available), (5) time between administration of antibiotics and surgery, (6) country and sites, and (7) rural or urban residence. In addition, we will perform an economic evaluation to determine if prophylactic antibiotics are cost-effective.

### Design and setting

The AIMS trial is a randomised, double blind, placebo-controlled multicentre study, with a health economic evaluation. The trial is set in a diverse range of hospitals across four countries, namely in Malawi at Queen Elizabeth Central Hospital, Zomba Central Hospital and Kamuzu Central Hospital; in Uganda at Mbale Regional Referral Hospital and Soroti Regional Referral Hospital; in Tanzania at Bagamoyo District Hospital, Mwananyamala Hospital and St Francis Hospital; and in Pakistan at Aga Khan University Main Hospital, Kharader Hospital, Garden Hospital, Hyderabad Hospital and Karimabad Hospital.

These participating countries were selected as this is a clinical problem that is of particular importance in low- and middle-income countries. Final country selection was based on the need for generalisability of the findings, prevalence of miscarriage surgery in these countries, importance of the clinical question in the participating country, existing research links, and research infrastructure to appropriately deliver the study to a high quality.

### Participants

The AIMS trial will include women with a spontaneous miscarriage under 22 weeks gestation undergoing surgical evacuation of the uterus (by manual vacuum aspiration, suction curettage or sharp curettage) that are willing and able to give informed consent, and are undergoing their first surgical evacuation in the current pregnancy (Fig. 1). Women having induced abortion of pregnancy, or with a septic miscarriage, evidence of infection or current febrile illness (temperature above 38 ºC) will be excluded. Women with an allergy or other contraindication to either of the antibiotics, or using antibiotics currently or within the 7 days preceding surgical evacuation, will also be excluded, as will women with conditions requiring immediate care, e.g. severe haemorrhage, women under 16 years of age or women requiring further surgical evacuation after the first surgical evacuation for the current pregnancy (multiple evacuations for the same pregnancy will not be included).

**Fig. 1 Fig1:**
[figure not shown]
Participant flow through trial

Potentially eligible patients will be approached in an adequate setting (i.e. outpatient clinics, wards, clinical assessment areas) and informed about the trial by an appropriately trained researcher or care provider. After all eligibility criteria has been confirmed, consent has been obtained and all baseline data gathered, participants will be randomised online via a secure internet facility to enable the allocation to remain concealed to the research staff and the care providers, as well as the participants, in a 1:1 ratio through an Integrated Trial Management System, to the investigational medicinal product or the placebo. Unblinding will only be possible by contacting the clinical trials unit. A minimisation procedure using a computer-based algorithm will be used to avoid chance imbalances in important stratification variables. Strata used in the minimisation will be age (below 35, or 35 years and above), gestation (below 12 weeks, or 12 weeks and above, or when the gestation is unclear), the type of miscarriage (either incomplete or missed), and HIV status (positive, proven negative, or unknown).

### Study intervention and comparison

The investigational medicinal products (IMPs) are doxycycline, as four 100 mg doxycycline hyclate encapsulated tablets, and metronidazole, as one 400 mg encapsulated tablet [14, 15]. The placebo tablets are encapsulated microcrystalline cellulose in the same format as the IMPs, identical in colour, shape and weight, produced and distributed by Sharp Clinical UK. Both healthcare provider and participant will be blinded to the allocation. The study medications will be taken approximately 2 hours before surgery. The IMP will be administered, with consent, under the direct observation of the clinician or researcher consenting the patient for the trial. Therefore, we do not anticipate compliance to be an issue unless the patient choses to withdraw their consent between randomisation and the IMP being taken. The choice of antibiotics was made after a careful review of the existing literature, a survey of preference, availability and affordability in the partner countries, and a review of other related evidence from induced abortion guidelines. Doxycycline is active against a broad range of Gram-positive and Gram-negative aerobic bacteria, including staphylococci, streptococci, and enteric Gram-negative bacteria. It is also active against *Chlamydia trachomatis* and *Neisseria gonorrhoeae*. Metronidazole is effective against anaerobic bacteria.

Doxycycline is associated with a substantially lower risk of life-threatening anaphylaxis compared with co-amoxiclav. Both of the study medicines are commonly used in low-income settings, and have low adverse event profiles. There is an extremely low risk of anaphylaxis, which was one of the reasons for the choice of these agents. However, should an anaphylactic reaction occur, all sites have facilities to manage this.

The use of other non-trial medications is at the discretion of the care-providing clinicians. Unblinding will only be performed in the event of a medical emergency in which treatment of the emergency requires knowledge of the actual drug received.

### Follow-up

Trial participants will be given multiple easy access routes to contact the research and clinical teams to report issues and seek advice and care. Women contacting the study or research team will be reviewed promptly. Reimbursement for potential telephone and transport costs will be offered to participants. Non-attendance at follow-up clinics will prompt telephone calls or others means of contacting the participant, which will be agreed at recruitment. If possible, contact will be made with the participant prior to the clinic to remind them through, for example, telephone calls or SMS text messages to prompt the reporting of any infection or other adverse events and follow-up clinic attendance.

### Withdrawal from study

A participant can be withdrawn from the trial if, in the opinion of the investigator, it is medically necessary. With premature withdrawal from the study, the study personnel will make every effort to obtain, and record, information about the reasons for discontinuation and any adverse events and to perform all safety assessments. A patient may voluntarily withdraw from participation in this study at any time. If the patient does not return for a scheduled visit, we will try to contact her. We will aim to document the reason for withdrawal and, when possible, all safety assessments will be performed. If a patient explicitly withdraws consent to have data recorded, their decision will be respected and recorded on the trial database. All communication surrounding the withdrawal will be noted in the patient’s records and no further data will be completed for that patient.

### Statistical analysis

The primary outcome is pelvic infection within 14 days of surgery. At the commencement of the study pelvic infection was defined (based on the CDC criteria and criteria used in previous studies) as two or more of (1) purulent vaginal discharge, (2) pyrexia > 38.0 °C, (4) uterine tenderness on examination and (4) a white cell count > 12 × 10^9^/L [14], with no other recognised cause of infection upon history taking and examination by the assessing clinician and/or study team (Table 1).

**Table 1 Tab1:** Primary outcome measure ascertainment

	Purulent vaginal discharge	Pyrexia	Tenderness	White cell count
Definition	Yellow, green, or offensive discharge	> 38.0 °C measured by infrared ear thermometry	Defined as a finding on examination of either (1) direct tenderness of the uterus, or (2) tenderness on displacement of the uterus, or (3) tenderness of the parametrium or (4) tender adnexal mass	White cell count greater than 12 × 10^9^/L
Excluded from the definition	Clear vaginal discharge		Upper abdominal pain	

An amendment was made to these criteria, after recruitment commencement, but without reference to study data, as it was observed by the examining clinicians (who were blinded to treatment allocation) that, for some participants, whilst only a single feature of pelvic infection was present, the symptoms were of sufficient severity that, in their clinical judgement, there was a need to provide treatment. After discussion with the independent trial steering committee it was decided that the diagnostic criteria by which pelvic infection was defined should be adjusted. Following this amendment, pelvic infection was diagnosed if the patient had two or more of (1) purulent vaginal discharge, (2) pyrexia > 38.0 °C, (3) uterine tenderness on examination and (4) a white cell count > 12 × 10^9^/L [16], with no other recognised cause of infection upon history taking and examination by the assessing clinician and/or study team, or one of the above features, with a clinically identified need to administer antibiotics for the treatment of presumed pelvic infection (Table 1: primary outcome measure ascertainment). The latter pragmatic criteria will be reported as the primary outcome, but the more specific strict clinical criteria for diagnosis of pelvic infection will also be clearly reported.

In cases where participants do not return for follow-up within the specified period of 2 weeks, follow-up until 28 days will be acceptable.

The secondary outcomes are overall general antibiotic use (not specifically for pelvic infection), each component of the primary outcome, death, hospital admission, unplanned consultations, blood transfusion, vomiting, diarrhoea, adverse events, anaphylaxis and allergy, duration of clinical symptoms (pain, additional analgesia, vaginal bleeding), and days before return to usual daily activities.

We are proactively seeking evidence of adverse events. Each participant will be asked, at each trial visit or interview, about hospitalisations, consultations with other medical practitioners, disability or incapacity, or any other adverse events.

The analysis will be by intention-to-treat. The risk ratio of women with pelvic infection in the active arm to the placebo arm will be calculated. This estimate will be adjusted for the minimisation variables although an unadjusted estimate will also be calculated as a sensitivity analysis.

In the first instance, analysis will be completed on received data only, with every attempt made to gather data on all subjects randomised, irrespective of compliance with the treatment protocol. To test the robustness of this initial analysis with respect to any missing data, missing responses will be simulated using a multiple imputation approach as a sensitivity analysis. Further sensitivity analysis will be performed assuming all non-responders had a pelvic infection.

Seven pre-specified subgroup analyses are planned to assess differential effects of antibiotic prophylaxis in (1) type of surgery (manual vacuum aspiration, suction curettage or sharp curettage; sharp curettage is associated with a higher incidence of pelvic infection when compared to suction curettage [3], so a greater effect of antibiotic prophylaxis may be seen in the sharp curettage group); (2) type of miscarriage (incomplete or missed; incomplete miscarriage may be associated with a higher incidence of pelvic infection when compared to missed miscarriage [3]); (3) gestational age (< 12 weeks or ≥ 12 weeks, when known; pregnancies of a greater gestational age may have a higher incidence of pelvic infection due to the additional complexities involved with the surgical procedure [3]); (4) HIV status (positive or negative, when results are available; participants that are HIV positive may be more likely to experience pelvic infection as they may be immunocompromised); (5) by time between administration of antibiotics and surgery (a reduced time interval between antibiotic administration and surgery, than that specified in the protocol, may result in a reduction in bio-availability and thus in effect reduction; the optimal maximum duration however is unclear); (6) by country and sites; and (7) rural or urban residence (the potential direction of effect is unclear in sub-group analyses (6) and (7)).

We will randomise 3400 women in total, which will give 90% power to detect a relative risk reduction of 0.4 (an RR of 0.6) (type I error rate, *P* = 0.05). A meta-analysis of 18 studies of prophylactic antibiotics used for induced abortion surgery was conducted to inform these calculations and found a pooled RR of 0.60 (95% CI 0.48–0.74) for the reduction of pelvic infection. We calculated sample sizes to detect this size of difference using various scenarios for the baseline risk (varying from 3% to 10%). The best available data for pelvic infection rates specific to spontaneous miscarriage originate from studies in the UK and USA, demonstrating a risk of pelvic infection of up to 6%; the risk of pelvic infection is likely to be higher in low-income countries, yet even for a baseline risk of, the 5% sample size of 3400 will provide over 80% power to detect a difference in primary outcome. Further sensitivity analysis will be performed assuming all non-responders had a pelvic infection.

Interim analyses of principal safety and effectiveness endpoints will be conducted on behalf of an independent Data Monitoring Committee (DMC). These will be considered together with a report of serious adverse events. A pragmatic approach to stopping rules was suggested by the DMC members with respect to interpreting the results of any interim analysis. Appropriate criteria of proof will therefore not be specified precisely, but an interim analysis difference equating to *P* < 0.001 (similar to a Haybittle–Peto boundary) may be needed to justify halting, or modifying, of the study prematurely. This criterion has the practical advantage that the exact number of interim analyses would be of little importance and there would only be minimal inflation of any overall type-I error rate regardless of how many interim analyses are performed, so no exact schedule needs to be proposed.

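### The second missing-data sensitivity analysis counts every non-responder in both arms as infected, a poor test of robustness once loss approaches or exceeds the event rate

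*Protocol article*

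**What the plan says.** In the protocol article, Statistical analysis section, the primary comparison is a risk ratio, active to placebo, first computed on received data only. Two sensitivity analyses for missing outcomes follow. The first is multiple imputation, introduced as a test of the robustness of the received-data result. The second reads "Further sensitivity analysis will be performed assuming all non-responders had a pelvic infection". The same sentence appears again at the end of the sample-size paragraph. It applies to all non-responders alike, whichever arm they were in.

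The figures that bear on its behaviour are in the same section and the abstract:
- Size: "A total of 3400 women will be randomised, 1700 in each arm".
- Power: 3400 women, "which will give 90% power to detect a relative risk reduction of 0.4 (an RR of 0.6"), with "type I error rate, *P* = 0.05".
- Baseline risk: calculations were made "using various scenarios for the baseline risk (varying from 3% to 10" per cent). UK and US data are described as "demonstrating a risk of pelvic infection of up to 6" per cent, with the remark that "the risk of pelvic infection is likely to be higher in low-income countries".
- Fallback: at a 5% baseline, "the 5% sample size of 3400 will provide over 80% power to detect a difference in primary outcome".

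No expected loss to follow-up is given.

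**The concern.** Pelvic infection is expected in a small minority of women. Counting every missing woman as infected adds a block of events that nobody observed, and at event rates of a few per cent that block can soon rival the real events. Two things follow. If loss is similar in the two arms, the same number of events is added to each and the RR shrinks toward 1, whatever the truth among the missing women. If loss differs, the difference in loss itself enters the RR as though it were a treatment effect.

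The missing-data scenario that most threatens a claimed benefit is that missing women on antibiotics had more infections than missing women on placebo. Giving both groups a risk of 100% cannot represent it. A sound benefit could therefore look fragile, or a modest attrition gap could look like benefit or harm, while the question a reader would ask about missing outcomes goes unanswered.

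**Working it through.** **Inputs.** From the article: 1700 per arm, RR 0.6, alpha 0.05, baseline risks 3% to 10%. Assumed: a two-sided test (sidedness is not stated), and a loss share m of 2%, 5% or 10%.

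**1. The plan's own power.** For two proportions p0 and p1 with n per arm, power = Φ[(|p0 − p1| − 1.96·SE0)/SE1], with SE0 from the pooled and SE1 from the separate variances. With n = 1700 and p1 = 0.6·p0 this gives 62.8% at 3% baseline, 84.5% at 5%, 90.6% at 6% and 99.1% at 10%. The statement of over 80% at 5% reproduces. The 90% figure reproduces at a baseline of about 6%, which the article does not state and is inferred here.

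**2. The rule with equal loss.** Each arm's risk becomes q = m + (1 − m)p. At 5% v 3% and m = 0.05:
- placebo: 0.05 + 0.95 × 0.05 = 0.0975
- active: 0.05 + 0.95 × 0.03 = 0.0785
- RR = 0.0785/0.0975 = 0.81

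Results for a true RR of 0.60, at losses of 2% / 5% / 10%:

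| Baseline | RR under the rule | Power under the rule | Power, received data |
|---|---|---|---|
| 3% | 0.76 / 0.86 / 0.91 | 39 / 25 / 16% | 62 / 61 / 58% |
| 5% | 0.72 / 0.81 / 0.88 | 68 / 50 / 33% | 84 / 83 / 81% |
| 6% | 0.70 / 0.79 / 0.86 | 78 / 62 / 44% | 90 / 89 / 87% |
| 10% | 0.67 / 0.74 / 0.81 | 97 / 92 / about 80% | 99 / 99 / 98% |

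Imputed events equal observed placebo events when m = (1 − m)p, that is m = p/(1 + p). At 5% baseline this is 0.05/1.05, or 4.8% loss. At 10% loss there are 170 imputed events per arm (1700 × 0.10), against about 77 observed on placebo (1530 × 0.05) and 46 on active (1530 × 0.03).

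**3. The rule with unequal loss.** No true effect, 5% risk in both arms, loss 7% active and 5% placebo:
- active: 0.07 + 0.93 × 0.05 = 0.1165
- placebo: 0.05 + 0.95 × 0.05 = 0.0975
- RR = 1.19; with the losses reversed, 0.84

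If those loss probabilities were the true ones, the power formula says the rule would show a significant difference about 43% of the time. With a true RR of 0.60 and the same 7% v 5% loss, active risk is 0.07 + 0.93 × 0.03 = 0.0979, so RR = 0.0979/0.0975 = 1.00.

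**4. What the rule does not show.** Take 5% baseline, true RR 0.60 and 5% loss in each arm. Keep missing placebo women at 5% risk and let a fraction f of missing active women be infected. Active risk is 0.95 × 0.03 + 0.05f = 0.0285 + 0.05f, and placebo risk stays 0.05.
- RR reaches 1 when f = (0.05 − 0.0285)/0.05 = 0.43.
- The upper 95% limit reaches 1 at about f = 0.16, using SE(log RR) = √[(1 − q0)/(n·q0) + (1 − q1)/(n·q1)] and ignoring imputation uncertainty.

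**The case against.** The case for leaving the plan alone has real substance.

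- Missing-equals-event is a simple, pre-specified extreme scenario. With balanced loss it is conservative for a superiority claim, and a benefit that survives it is informative. This stands, and is why the scenario need not be deleted.
- A reader might infer that the rule always forces the RR toward 1. It does so only when loss is similar by arm; step 3 shows it moving either way.
- A reader might infer that a true benefit would usually look fragile, or that the rule cannot test robustness at all. The article does not support that. Its baseline range reaches 10%, it expects risk above the UK and US figure, and at 10% baseline with 5% loss power under the rule is 92%. At 1% to 2% loss and 5% to 6% baseline the RR moves only to about 0.66 to 0.72. Equally, 3% lies within the stated range, and there the rule performs badly.
- A 7% v 5% loss gap is not trivial: with 1700 per arm its own z is about 2.46. The resulting RR of 1.19 has an expected z of about 1.79, short of significance on average. Double blinding and a single directly observed dose make differential loss less likely, and the follow-up arrangements (reminders, reimbursement, tracing, acceptance up to 28 days) should keep loss down. This limits how likely the problem is, not how the rule behaves if it arises.
- Tipping-point detail often belongs in an analysis plan, which is not shown. The point here, however, concerns a rule that the article does state. The multiple imputation is described without any departure from missing at random, so the all-infected rule is the only stated analysis with an explicit non-random assumption.

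**Conclusion.** The point holds as a weakness of one secondary sensitivity analysis. The rule is a poor check on missing-data bias when the share lost is close to or above the infection risk: at 5% baseline and 5% equal loss, half or more of the placebo events are imputed (85 against about 81 observed) and power falls from 83% to about 50%. With unequal loss its result partly measures attrition. At no loss rate does it examine missing active women faring worse than missing placebo women.

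The size depends on loss rates, which are assumed throughout, and on where the baseline falls within 3% to 10%. At high baseline or very low loss the damage is modest. It would be wrong to conclude that the primary result is compromised or that missing data are otherwise unexamined: the received-data analysis is untouched, multiple imputation is also planned, and no decision in the article hangs on this scenario. It is a worthwhile, inexpensive improvement.

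**What to change.** Before unblinding, add an arm-specific delta-adjusted or tipping-point analysis built on the planned multiple imputation. Vary the infection risk among missing women separately in each arm, starting from the observed arm risks. Include the case against the drug, in which missing active women do worse than missing placebo women. Report how far the missing women would have to depart from the observed ones before the conclusion changes, and name this as the main missing-not-at-random analysis.

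Keep the all-infected scenario only as a labelled extreme case, and always show it with the number lost in each arm so that a reader can see how much of the RR comes from attrition.

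The cost is a change of wording, a little more programming and a slightly longer report. No new data and no change to the sample size are needed.
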